### Secondary outcomes

Symptoms of PTSD at 7 and 30 days will be measured by the IES. PTSD will be measured at 90 days using the Post-traumatic Stress Disorder Checklist for Diagnostic and Statistical Manual of Mental Disorders (DSM-5).^30 31^ Anxiety and depression scores will be measured at 7, 30, and 90 days by the Hospital Anxiety and Depression Scale (HADS), which has been validated in French.^32^,^34^ The relatives’ experiences of the announcement will be collected at 7 days through a questionnaire investigating feelings and experience. The presence of at least one work absenteeism related to the ED visit as well as the number of days of work absenteeism will be assessed within 90 days of the announcement.

### Measurement of HCP outcomes

Satisfaction with the training received will be evaluated by an ad-hoc questionnaire 90 days after training. Assertiveness in communication will be measured at baseline and at 90 days using the Cungi and Rey scale.^35^ Self-confidence will be assessed at baseline and at 90 days by an ad hoc questionnaire. Real-life stress levels in the work environment will be evaluated at baseline and at 90 days using the Karasek scale.^36 37^ Behavioural changes will be collected after training by an ad hoc questionnaire, and experience of the announcement will be collected by individual semistructured interviews 90 days after the training.

### Implementation process evaluation

Elements that are independent of the intervention that may have modified the implementation or effect of the intervention will be studied using quantitative and qualitative approaches. Regarding training delivery, the number and profile of HCP trained in the simulation centre and in situ will be collected. Regarding protocol implementation, the fidelity of the intervention deployed and the adaptations made will be recorded. The participation and satisfaction of HCP regarding the training will be collected. The proportion of announcements during which strong emotional reactions or conflicts/complaints arised as well as the unexpected effects of using the announcement protocol on the relatives, HCP and EDs will be collected by questionnaire and during semistructured interviews. The organisational factors in the EDs that can influence the deployment of the intervention will be researched.

### Data collection

Inclusion began in January 2024 and will end in September 2025, with the last patients included being monitored until the end of December 2025. Data will be collected from the ED medical charts by research assistants. For each relative included in the trial, a case report form will be completed with his/her characteristics (age, sex) and the characteristics of the patient.

Relatives will be contacted at 7, 30 and 90 days to collect outcomes. This will be done by telephone by a psychologist of the study coordinating centre. The data collected are listed in online supplemental table 1.

### Data management

All information required by the protocol will be recorded in an electronic case report form (eCRF). This eCRF, specific to the study, will be developed by a data manager from the Hospices Civils de Lyon on the Ennov Clinical software (V.8.2.50).

The data set will be computerised in a coded way, in accordance with the law for data protection and freedom of information (Article L.1121-3 of the French Public Health Code). The study families will be identified by a unique study inclusion number and by the first initial of their surname and of their given name.

Data will be entered, as soon as they are collected, by the authorised persons (investigator and personnel recorded on the delegation log) according to the law for data protection and freedom of information.

Access to the data will be restricted to the authorised persons only. Authentication will be made using passwords, which will be regularly changed. The investigators and clinical research assistants of an investigating centre will only have access to the data for their patients and will enter the data directly into the eCRF using a secured website. The investigator will be responsible for the reliability of the data entered. Throughout the length of the study, the data will be stored in an ISO 27001-certified data centre and backed up daily.

### Sample size

A mean IES of 33 is expected at 90 days during the control periods (SD of 9) and a relative reduction of 12% of the mean score is expected with the intervention. Under thess hypotheses, for a 90% power and a 5% two-sided alpha level, 216 families would be necessary. By considering an intraclass correlation coefficient of 0.35, 9 EDs divided into 4 groups and 15% of loss to follow-up, a total of 538 families will be necessary.

### Recruitment

The nine participating centres were chosen for their high inclusion potential with over 300 000 annual ED admissions and approximately 600 decisions of withholding or withdrawing life-sustaining treatments per year. In a previous study, a mean of six patients were included per month in two of the participating centres.^38^ Based on this experience and given the similar activity of the other investigating centres, recruiting three families per month and per centre seems feasible.

### Statistical analysis

The IES Score will be analysed by a linear mixed effect model. It will consider as fixed effect, the intervention (period with or without the intervention), the measurement time point (7, 30 and 90 days), and an interaction between time point and period. The model will also be adjusted on the following factors:

Regarding the patient: age, institutionalised patient, advance directives, death of the patient during the 90 days.Regarding the relatives: age, sex, relationship with the patient, lifestyle (single or in a relationship), frequency of contact with the patient over the past 6 months, history of psychological or psychiatric care, religious beliefs.Regarding the ED at the time of the announcement: work overload, doctor/nurse/patient ratio in the ED at the time of the announcement.

The model will include as random effect, a random intercept by ED and a random intercept and slope by family nested in the ED level. The effect of the intervention at 90 days will be recalculated from the coefficients of the model; it will be quantified by the difference of mean with the associated 95% CI and tested by a Wald test. A period effect will be tested in the model. A secondary analysis for the primary endpoint will be performed by considering IES as a binary variable, a value above 30 indicating a high risk of PTSD. The analysis will be similar to the one previously described, but performed using a mixed effect logistic regression model.

The analysis of PTSD at 7 and 30 days will be performed by calculating the effect of the intervention from the coefficients of the aforementioned model.

The analysis of anxiety and depression will be performed similarly to one of the primary endpoint and will focus specifically on the effect of the intervention at day 7 and on the effect of the intervention on the slope. A binary analysis will also be performed, by considering anxiety or depression when the HADS scores are above 8.

The analysis of PTSD symptoms at 90 days will be performed by a mixed effect logistic regression model, considering only the ED as random intercept. The comparison of the proportion of relatives with at least one work absenteeism will be performed by a mixed effect logistic regression model. The percentages of relatives for whom the announcement was considered smooth will be compared. A threshold of 0.05 will be considered significant. Analyses will be performed using R and SAS software (version 9.4).

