**Methods and analysis:**

The DISCUSS trial is a multicentre stepped-wedge cluster randomised study and will be conducted at nine EDs in France. A standardised intervention based on human simulation will be codesigned with partner families and implemented at three levels: the relatives, the healthcare professionals (HCP) and the EDs. The intervention will be compared with a control based on treatment as usual. A total of 538 families are planned to be included: 269 in the intervention group and 269 in the control group. The primary endpoint will be the symptoms of post-traumatic stress disorder (PTSD) at 90 days. The secondary endpoints will be symptoms of PTSD at 7 and 30 days, diagnosis of PTSD at 90 days and anxiety and depression scores at 7, 30 and 90 days. Satisfaction regarding the training, the assertiveness in communication and real-life stress of HCPs will be measured at 90 days.

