### Intervention implementation

The intervention will then be deployed at three levels. At the level of the HCP (physicians and nurses), the intervention will consist in a two-step human simulation training approach. First, two pairs of HCP (one physician and one nurse) will be trained in a simulation centre by a trainer specialised in simulation concerning decisions of withholding or withdrawing life-sustaining treatments. The trained HCP will then implement the training in situ in the ED with the help of the specialised trainer. The scenarios used in the human simulation training will be constructed during the first phase with the partner families based on their experiences. The intervention will also include video testimonials from partner families and a training manual including all the objectives and skills targeted by the training, which will be made available electronically to all HCP. At the level of the relatives, an information booklet on the decision-making process for withdrawing or withholding life-sustaining treatments and end-of-life care in the context of EDs, codeveloped with the partner families, will be given to the relatives included in the study. Finally, at the level of the ED, changes will be made to provide a dedicated room for the announcement. Time will be allocated specifically for making the announcement, which will be made by a team of HCP (a physician and a nurse).

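### The primary IES model adjusts for patient death within 90 days, an event after the announcement that the intervention could affect; this can bias the estimate away from the stated total effect

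*Protocol article*

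**What the plan says.** The main objective (Objectives) compares relatives' PTSD symptoms 90 days after the announcement between announcements made after implementation and those made under usual practice. That is a total effect of the intervention.

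The Statistical analysis section estimates it from a linear mixed model of IES at days 7, 30 and 90, with intervention, time point and their interaction as fixed effects. The 90-day difference is derived from the coefficients and tested by a Wald test. The model is also adjusted for a fixed list, whose patient-level part reads: "Regarding the patient: age, institutionalised patient, advance directives, death of the patient during the 90 days". The ED-level part reads: "work overload, doctor/nurse/patient ratio in the ED at the time of the announcement".

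The day 7 and day 30 effects come from this same model. The binary IES analysis is described as similar, and so are the anxiety and depression analyses, which focus on day 7 and the slope. The section gives no reason for adjusting on death and describes no analysis without it.

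**The concern.** Every other patient-level adjuster in the list is settled before the announcement. Death within 90 days is not: it can occur on any day from the announcement to the day the endpoint is measured.

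Two links make this matter. First, the intervention could act on death or its timing. It retrains the staff who announce these decisions, gives relatives a booklet on the decision-making process and end-of-life care, and sets aside a room and time (Intervention implementation). The Introduction says families are asked to take part in these decisions. Second, the Introduction (Impact on relatives) reports stronger PTSD symptoms among relatives of deceased patients, from intensive care data.

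If both links operate, adjustment removes the part of the effect that passes through death. If death and distress also share unmeasured causes, adjustment opens a further non-causal path between intervention and outcome. The coefficient then need not equal the effect in the main objective. Separately, a death on day 60 would help to explain a day 7 score, which makes the day 7 and day 30 estimates hard to interpret.

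**Working it through.** **1. The plan's own figures.** The target is "a relative reduction of 12% of the mean score is expected with the intervention", so 0.12 × 33 = 3.96 points. With SD 9, 90% power and two-sided 5%:

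- Unadjusted total: 2 × 2 × (1.960 + 1.282)² × 9² / 3.96² = 217.1, against the stated 216.
- Stepped-wedge design effect (Woertman form, 4 steps, one baseline period, one measurement period per step, ICC 0.35, an assumed 10.2 families per ED-period): [1 + 0.35 × 50] / [1 + 0.35 × 29.6] × 3 × 0.65 / (2 × 3.75) = 1.6285 × 0.26 = 0.4234.
- 0.4234 × 5 periods × 216 = 457.3, and 457.3 / 0.85 = 538, as stated.

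Neither figure depends on the covariate list, so the sample size is not at issue.

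**2. What adjustment does.** In a linear model, let Δp be the change in the probability of 90-day death caused by the intervention, and β the death coefficient in the adjusted model. Then

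adjusted estimate = total effect − β × Δp.

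The shift is zero if Δp = 0, and its sign follows the sign of Δp. β contains any effect of death itself plus whatever death picks up from shared causes.

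**3. Illustration.** None of these inputs is in the documents; all are assumed. The direct effect of the intervention is −3.96; death adds 5 IES points; 60% of patients die by day 90 in control periods; the intervention changes the log-odds of death by +0.5 or −0.5; an unmeasured cause raises the log-odds of death by 1 and IES by 3 points per SD. By numerical integration β is about 7.5: 5 from death itself and about 2.5 from the shared cause.

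| 90-day death, control → intervention | Total effect | Death-adjusted | Shift | % of 3.96 |
|---|---|---|---|---|
| 60% → 69.5% | −3.96 + 5 × 0.095 = −3.49 | −4.20 | 0.71 away from null | 18 |
| 60% → 49.8% | −3.96 − 5 × 0.102 = −4.47 | −3.71 | 0.76 towards null | 19 |
| 60% → 60% | −3.96 | −3.96 | 0 | 0 |

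In the first two rows the adjusted figure is neither the total effect nor the direct effect of −3.96. If death has no effect of its own and only the shared cause acts, the shift is 0.24 to 0.25 points. For a 5-point change in death it is 7.5 × 0.05 = 0.375, about 9.5% of target.

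**4. A simpler range without a shared cause.** The shift is Δp × (IES difference by death), with the difference assumed to be 2 to 6 points. The power column applies if the total effect is 3.96, the shift is towards the null and the standard error is unchanged: Φ[(3.96 − shift)/3.96 × 3.242 − 1.960].

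| Δp | Shift (points) | % of 3.96 | Nominal 90% power becomes |
|---|---|---|---|
| 0 | 0 | 0 | 90% |
| 5 points | 0.10 to 0.30 | 2.5 to 7.6 | 88.5 to 85% |
| 15 points | 0.30 to 0.90 | 7.6 to 22.7 | 85 to 71% |

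**The case against.** **The path through death may be weak.** Relatives enter at the first announcement of a decision already reached, and the trial has no objective of changing mortality. This stands as a reason to say that adjustment can bias the result. A reader might infer that the primary estimate is certainly biased; the documents do not support that, since they report no effect of the intervention on death.

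**The size is modest and of unknown sign.** The planned power implies a standard error of about 3.96 / 3.242 = 1.22, so a shift of 0.7 to 0.8 is about 0.6 standard errors, and it may go either way. This is fair, but a shift of unknown sign in the primary estimate cannot be corrected afterwards.

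**The timing argument concerns secondary results.** The primary contrast is at day 90, so the later-event objection bears on the day 7 and day 30 IES effects and on HADS. That is correct.

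**Death may stand in for severity.** Families are recruited within periods and are not individually randomised, and the list has no other direct marker of patient severity. Death could absorb some difference in case mix between periods. This stands in part, and it is the reason to keep a death-adjusted analysis alongside. It does not make death a clean adjuster, because the proxy is itself measured after exposure.

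**Workload and staffing.** A reader might extend the point to these terms, since the intervention allocates time and a physician-nurse team to the announcement. The documents do not support that. The terms are defined as ED conditions when the announcement is made and precede every outcome. The ED-level changes concern the room, time and team for the announcement, and no change in overall load or staffing is described. Adjusting for such context is reasonable in a stepped wedge, where exposure is tied to calendar time.

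**Conclusion.** The point holds for 90-day death only. The primary IES model, and the binary IES and HADS models patterned on it, condition on an event that follows the announcement, that the intervention could affect and that is linked to the outcome. The 90-day estimate can therefore depart from the total effect in the main objective, and the day 7 and day 30 estimates are conditioned on later events.

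The illustrated 0.7 to 0.8 points rests on a change of about 10 points in death, 5 IES points for death and a shared cause, none of which the documents give. The defensible statement is a range that starts at zero and grows with the change in death.

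**What to change.** Delete death of the patient during the 90 days from the adjustment list of the primary IES model, and state that the binary IES and HADS models also omit it. Report the same models with death added as a labelled sensitivity or exploratory analysis, together with 90-day death by period type, so that readers can see whether death moved. Keep the other listed adjusters, including the workload and staffing terms. Make the change before outcomes are compared between groups, so that it cannot look data-driven.

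The cost is a wording change. The figures of 216 and 538 families are unaffected. There may be a small loss of precision if death strongly predicts IES, and the primary model loses a rough proxy for patient severity, which the sensitivity analysis retains.

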## Methods and analysis

### Study design

The DISCUSS trial is a multicentre stepped-wedge cluster randomised study, which will be conducted at nine EDs in France. The nine EDs will be arranged into four groups, each group thus being composed of two to three EDs. The trial will be performed in five steps, and each group of clusters will be randomly assigned to one step. After a preintervention period (control), the intervention will be sequentially implemented in the groups at different times, according to a random allocation sequence generated by computer by the biostatistical team in charge of data analysis and blinded to group composition. All clusters will eventually receive the intervention (figure 1).

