The strengths of this study are that it uses a mixed methodology including a qualitative component to study the experiences of HCP and families in greater depth. In addition, the protocol uses a patient-centred research approach by including partner families in the first phase of the study. These partner families, having experienced an announcement of a decision to withhold and withdraw life-sustaining treatments, will be able to help develop and validate the training (booklet, scenario).

The chosen methodology is a stepped-wedge randomised controlled trial to assess the effectiveness of this complex intervention. This design provides a high level of evidence while adopting the pragmatic approach needed to study the implementation of training in practice. One of the strengths of this methodology is that it makes it possible to analyse the effect of time and to consider each ED as its own control, therefore taking into account the effect differences between clusters. In this case, the effect differences are potentially significant due to the differences in size and organisation of the participating EDs, making it the methodology of choice compared with a parallel cluster trial. In addition, this method will reduce the risk of contamination during the study, since each ED undergoes the training at the end of the study.

The proposed protocol may contribute to improve the announcement of decisions to withdraw or withhold life-sustaining treatments and reduce the impact of these announcements on relatives. It will also strengthen relational skills for HCP, improve their relationships with families and enhance patient and family-centred care. In case of positive results, the standardised intervention may be transferred to other EDs.

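### The primary mixed model gives each ED one random intercept that is constant over time; if ED effects drift between periods, the day-90 confidence interval is too narrow at the planned ICC of 0.35.

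*Protocol article*

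**What the plan says.** Under Statistical analysis, the protocol article analyses the IES score with a linear mixed model. Its fixed effects are intervention, measurement day (7, 30, 90), their interaction, and a list of patient, relative and ED covariates. The random part is "a random intercept by ED and a random intercept and slope by family nested in the ED level". For the day-90 effect, "it will be quantified by the difference of mean with the associated 95% CI and tested by a Wald test". A period effect is to be tested in the model. No random effect varies by ED and calendar period, and no intervention effect varies by ED.

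Under Study design, nine EDs form four groups: "The trial will be performed in five steps, and each group of clusters will be randomly assigned to one step". Under Data collection, inclusion runs from January 2024 to September 2025. Under Sample size, clustering enters as one value: "intraclass correlation coefficient of 0.35, 9 EDs divided into 4 groups and 15% of loss to follow-up, a total of 538 families will be necessary".

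**The concern.** A stepped-wedge trial estimates its effect largely by comparing later with earlier periods inside the same ED. A constant ED intercept drops out of that comparison almost entirely. Anything that moves one ED up or down from one period to the next does not drop out: it adds directly to the error of the estimate. The stated model has no term for such movement. It treats the spread of ED-period means as sampling error among families only, apart from a shift common to all EDs.

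This is a choice the article makes, since it spells out the random effects. At stake are the width of the primary interval and the 5% error rate of the primary test. The high planning ICC matters because even a small share of a large ED variance is considerable beside the sampling error of a mean of ten families.

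**Working it through.** **Inputs from the protocol article.** Control mean 33, SD 9 (variance 81), 12% relative reduction (0.12 × 33 = 3.96 points), 5% two-sided alpha, 90% power, ICC 0.35, nine EDs in four groups, five steps, 15% loss, 538 families.

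**Assumptions, not in the document.** One baseline period and four switches; EDs split 3, 2, 2, 2; fixed period effects kept in the model; a ratio *r* of between-period to within-period ED correlation of 1, 0.95, 0.9 or 0.8; an SD of ED-specific intervention effects of 0, 1, 2 or 3 points.

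**Step 1: the plan's own figure.**
- Unclustered total: 4 × (1.960 + 1.282)² × 81 / 3.96² ≈ 217, against the stated 216.
- Stepped-wedge design effect with *m* = 10.16 families per ED-period: [1 + 0.35(5*m* − 1)] / [1 + 0.35(3*m* − 1)] × 3(1 − 0.35) / [2(4 − 1/4)] = 18.43 / 11.32 × 0.26 = 0.4234. Over five periods this is 2.117.
- 216 × 2.117 ≈ 457 analysed families, and 457.3 / 0.85 = 538.

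The 538 therefore reproduces with an ED effect that is constant over time (*r* = 1).

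**Step 2: standard error with and without drift.** The ED variance is 0.35 × 81 = 28.35. The family variance is 0.65 × 81 = 52.65, or 52.65 / 10.16 = 5.18 for an ED-period mean. The model takes the covariance of an ED's five period means as 28.35 **J** + 5.18 **I**. With drift it is 28.35*r* **J** + [28.35(1 − *r*) + 5.18] **I**. The generalised least squares estimator built on the first form has a true variance given by the sandwich formula under the second. Type I error is 2Φ(−1.96 × model SE / true SE).

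| *r* | extra ED-period variance | model SE | true SE | type I error |
|---|---|---|---|---|
| 1 | 0 | 1.223 | 1.223 | 5.0% |
| 0.95 | 1.42 | 1.223 | 1.376 | 8.2% |
| 0.9 | 2.84 | 1.223 | 1.514 | 11.3% |
| 0.8 | 5.67 | 1.223 | 1.757 | 17.2% |

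Hand check at *r* = 0.9: 1.223 × √[(5.18 + 2.84) / 5.18] ≈ 1.52.

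**Step 3: smaller ICC, *r* = 0.9.** ICC 0.10: SE 1.385 against 1.450, type I error 6.1%. ICC 0.05: 1.371 against 1.395, 5.4%.

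**Step 4: simulation of the stated model.** REML fits with days 7, 30 and 90, an ED intercept, family intercept and slope, fixed periods and a Wald z test; 10 families per ED-period, no covariates, 800 trials per scenario, assumed split of within-family variance. At ICC 0.35, type I error was 4.9%, 8.6%, 13.3% and 18.6% for *r* = 1, 0.95, 0.9 and 0.8, with coverage of 95.1%, 91.4%, 86.7% and 81.4%. At ICC 0.10 and *r* = 0.9 it was 7.1%. Monte Carlo error is about 0.8 points near 5% and 1.4 points near 18%.

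**Step 5: ED-specific intervention effects (*r* = 1, ICC 0.35).** For SDs of 1, 2 and 3 points, type I error is 5.9%, 8.7% and 13.3% analytically, and 6.8%, 10.9% and 15.4% simulated.

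**Step 6: after adding a random ED-by-period intercept.** For *r* = 0.95, 0.9 and 0.8, simulated type I error is 6.1%, 6.5% and 7.9% with z, and 5.2%, 5.2% and 7.1% with a t reference on just over 30 degrees of freedom. With ED-specific effects of SD 2 or 3 it is still 8.0% and 8.6% with z.

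**Step 7: power of the correctly specified analysis.** Its SE is 1.375, 1.509 and 1.739 for *r* = 0.95, 0.9 and 0.8. Φ(3.96 / SE − 1.96) gives 82%, 75% and 62%.

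**The case against.** The strongest reply is that nothing in the document shows ED effects to drift. That stands. The ratio and the effect SD are assumptions, and with neither kind of variation the stated model holds its level. The model also adjusts for workload and staffing ratio at the time of the announcement, which could absorb part of any drift. The calculations carry no covariates, so they may overstate what remains.

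Three stronger readings are tempting, and the document does not support them.

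- *A Wald test with nine EDs is itself invalid.* The simulated 4.9% at *r* = 1 was obtained with exactly that. A Wald-type test can also use a small-sample reference, and the degrees of freedom may properly be left to the analysis plan.
- *The protocol concedes that the intervention works differently across EDs.* The Discussion says "the effect differences are potentially significant due to the differences in size and organisation of the participating EDs", but in explaining why each ED serves as its own control. That arrangement deals with differences in level between EDs, which the random intercept already covers. The staff turnover mentioned there concerns sustaining the intervention.
- *An ineffective intervention would be declared effective too often, whichever kind of variation is present.* Only the drift scenarios describe an intervention with no effect. In the effect-SD scenarios it has real ED-level effects that average zero.

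**Conclusion.** The point holds conditionally. The article fixes a random structure that is valid only if ED effects are stable over about 20 months and the intervention effect is common to all EDs. At the planning ICC of 0.35, modest drift (ratio 0.95 to 0.8) raises type I error to about 8 to 17%, and ED-specific effects of SD 2 points raise it to about 9 to 11%. If the true ICC is nearer 0.05 to 0.10 with ratio 0.9, the analytic excess is about one percentage point or less. A reader might infer that the planned interval is too narrow in any event; it is not, because without such variation it covers at 95%. The figures also assume that fixed period effects are retained, whereas the article says only that a period effect will be tested.

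**What to change.** Before outcomes are analysed:

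- Add a random ED-by-calendar-period intercept to the primary linear mixed model, alongside fixed period effects.
- With that model, test the day-90 contrast and build its interval using a small-sample reference such as Kenward-Roger, available in the SAS software already named. This accompanies the added variance term and does not replace it. Kenward-Roger itself was not simulated here.
- Run a sensitivity analysis with a random intervention effect by ED, because the ED-by-period term alone does not fully cover effects that differ between EDs.
- Carry the ED-by-period term into the mixed logistic models where it can be estimated.

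No extra data are needed. The cost is a wider interval. Simulated power at the planned size is about 85% if there is no ED-by-period variation. If there is, power is about 82%, 75% or 62% at ratios of 0.95, 0.9 or 0.8, against the planned 90%. The latter loss comes from the variation itself, and the present model would leave it unreported.

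### The primary model does not commit to keeping calendar period: the plan says only that a period effect will be tested

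*Protocol article*

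**What the plan says.** **Design.** Study design sets the grouping: "The nine EDs will be arranged into four groups, each group thus being composed of two to three EDs". Roll-out takes five steps in a randomised order of groups, and no ED stays in control to the end: "All clusters will eventually receive the intervention". Under Data collection: "Inclusion began in January 2024 and will end in September 2025", a span of about 21 months.

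**Primary model.** The Statistical analysis section says: "It will consider as fixed effect, the intervention (period with or without the intervention), the measurement time point (7, 30 and 90 days", followed by their interaction and a long list of patient, relative and ED covariates. Time in this list is follow-up day. Period in this list is intervention status. The random effects are an ED intercept and a family intercept and slope within ED. The 90-day effect is derived from the coefficients of that model.

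**Calendar time.** After the Wald test for the 90-day effect comes one sentence: "A period effect will be tested in the model". It does not give the coding of period, what follows from the test, or which model supplies the reported effect.

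**Other outcomes.** Binary IES and HADS are analysed along the lines of the primary model. For PTSD at 90 days and absenteeism a mixed logistic model is named without a calendar term. For the experience of the announcement the text says only "The percentages of relatives for whom the announcement was considered smooth will be compared".

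**The concern.** Every ED gives its control data first and its intervention data later. A change in IES over 21 months that is common to all EDs (case mix, staffing, other training, public debate on end of life) therefore runs in the same direction as exposure within each ED. A random ED intercept removes stable differences between EDs, but not a trend they share. Only a calendar term separates that trend from the intervention.

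The article fixes the model in detail, down to religious beliefs and staffing ratios, yet leaves the one adjustment that the design requires to a test with no stated consequence. The primary estimate could then come from a model with or without calendar period, and the choice could be made after the data are seen. The double use of the word period adds to the doubt about what is to be tested.

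**Working it through.** **Inputs.** From Sample size: control mean 33, SD 9, 12% relative reduction, 90% power, 5% two-sided alpha, 216 families before adjustment, ICC 0.35, 9 EDs in 4 groups, 15% loss, 538 in total. From Study design: 4 groups and five steps, read as 5 periods. My assumptions: equal periods; group sizes 3, 2, 2, 2 (2, 2, 2, 3 gives the same SEs and bias); equal numbers per ED-period; day-90 score only; known variances; no ED-by-period random effect; no covariates. The documents give no secular trend, so the drifts are illustrative.

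**Step 1: the plan's own sample size.**
- Target difference: 0.12 × 33 = 3.96 points.
- Unadjusted total: 4 × 81 × (1.960 + 1.282)² / 3.96² = 217.1, against 216 stated.
- Stepped-wedge design effect of Woertman, which rests on a model with fixed calendar periods, with k = 4 steps, one measurement per period and n families per ED-period: DE = [1 + ρ(kn + n − 1)] / [1 + ρ(kn/2 + n − 1)] × 3(1 − ρ) / [2(k − 1/k)].
- With ρ = 0.35 and n = 10.16: DE = 18.43 / 11.32 × 0.26 = 0.4234.
- 216 × 0.4234 × 5 periods = 457.3 evaluable families, which agrees with 9 × 5 × 10.16. Then 457.3 / 0.85 = 537.9, the stated 538.

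**Step 2: the estimate with and without calendar period.** Generalised least squares on the 45 ED-period means (457/45 = 10.16 families each), with a random ED intercept:

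| Model | SE of intervention effect | Bias per 1 point of drift per period |
|---|---|---|
| No period term | 0.76 | 2.48 |
| Period as 5-level fixed effect | 1.22 | 0 |

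Power with period in the model: Φ(3.96/1.22 − 1.96) ≈ 90%. At ICC 0.01 the bias without period is still 2.1.

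**Step 3: no true effect, steady downward drift.** Type I error at a nominal 5%. The first three result columns are analytic or from 40,000 simulated trials; in the pre-test columns, period is kept only if its 4-df Wald test has p < 0.05.

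| Drift per period | Never in model | Kept only if significant | Always in model | Test detects drift | Mean bias, kept only if significant |
|---|---|---|---|---|---|
| 0.25 | 13% | about 13% | 5% | 7% | −0.51 |
| 0.5 | 37% | 33% | 5% | 15% | −0.88 |
| 0.75 | 68% | 49% | 5% | 31% | −0.99 |
| 1.0 | 90% | about 45% | 5% | 52% | about −0.8 |
| 1.5 | 99.8% | 13% | 5% | 90% | about −0.2 |

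The largest mean bias under the pre-test is 0.99 / 3.96 = 25% of the target effect. With no period term, a drift of 0.5 gives 2.48 × 0.5 = 1.24 points, or 31% of the target. These two bias figures belong to different strategies and should not be combined.

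The pre-test figures depend on the form of the test. With a 1-df linear trend, type I error for drifts of 0.25 to 1.0 is about 14%, 30%, 36% and 26%.

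**The case against.** The article contains no rule for dropping period. A term tested in a model is in that model when it is tested, and it may well stay there. If it does, the shared trend is removed and the primary analysis is sound. The Discussion also counts among the strengths of the design that "it makes it possible to analyse the effect of time and to consider each ED as its own control", so the authors plainly have time in mind. This stands. A reader might infer that any secular trend will be credited to the intervention, but that holds only if period is never fitted, which the text does not say. A reader might equally take test-then-drop to be the plan, which the text does not say either. Even under that rule large drifts are mostly caught.

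Three further points stand in part. Binary IES and HADS follow the primary model, so they inherit its period sentence and are not separate omissions. For the comparison of smooth announcements no method is named, so it cannot be called unadjusted. The Sample size section does not name its formula; that 538 rests on fixed periods is inferred from the close match. It is also possible that the planned adjustment for work overload and staffing ratio would absorb part of a trend, but no measured covariate guarantees this.

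What the objection does not remove is the missing commitment. An article may leave detail to an analysis plan, but this one sets out the model and states testing as its only handling of calendar time.

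**Conclusion.** The point holds as a defect of specification in the primary analysis. Calendar period is not among the listed fixed effects, its retention is not stated, and the word has two meanings in one paragraph. The consequence depends on which reading is applied. Always kept: no bias from a trend common to all EDs, and type I error of 5%. Kept only when significant: type I error up to about 49% and mean bias up to about 1.0 point for moderate drifts. Never kept: 2.48 points of bias per point of drift per period, and an SE of 0.76 where 1.22 is warranted.

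These sizes rest on the simplified layout and the illustrative drifts in the working. The direction of the argument does not: exposure is tied to calendar time by the design itself. The documents do not support the stronger claim that the planned estimate is a plain before-after comparison.

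**What to change.** Before the analysis, replace the sentence on the period effect with a statement of this kind: calendar period (5 levels) is a categorical fixed effect in the primary IES model, from which the 90-day intervention effect is taken, and it is retained whatever its p-value. A test of period may still be reported, but nothing should depend on it.

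Say that the same term carries over to the binary IES and HADS analyses modelled on the primary one. Name it also for PTSD at 90 days, absenteeism and the comparison of smooth announcements. Call the exposure variable intervention throughout, including in the interaction with follow-up time, and reserve period for calendar period.

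The cost is a few lines of text. No new data are needed beyond the date of inclusion. No extra families are needed either: with 457 evaluable families and period in the model, power for 3.96 points is about 90%, the level planned.
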